## Abstract

**Background:**

Thermal ablation of colorectal liver metastases (CRLM) may result in local progression, which generally appear within a year of treatment. As the timely diagnosis of this progression allows potentially curative local treatment, an optimal follow-up imaging strategy is essential. PET-MRI is a one potential imaging modality, combining the advantages of PET and MRI. The aim of this study is evaluate fluorine-18 deoxyglucose positron emission tomography (FDG) PET-MRI as a modality for detection of local tumor progression during the first year following thermal ablation, as compared to the current standard, FDG PET-CT. The ability of FDG PET-MRI to detect new intrahepatic lesions, and the extent to which FDG PET-MRI alters clinical management, inter-observer variability and patient preference will also be included as secondary outcomes.

**Methods/Design:**

Twenty patients undergoing treatment with radiofrequency or microwave ablation for (recurrent) CRLM will be included in this prospective trial. During the first year of follow-up, patients will be scanned at the VU University Medical Center at 3-monthly intervals using a 4-phase liver CT, FDG PET-CT and FDG PET-MRI. Patients treated with chemotherapy <6 weeks prior to scanning or with a contra-indication for MRI will be excluded. MRI will be performed using both whole body imaging (mDixon) and dedicated liver sequences, including diffusion-weighted imaging, T1 in-phase and opposed-phase, T2 and dynamic contrast-enhanced imaging. The results of all modalities will be scored by 4 individual reviewers and inter-observer agreement will be determined. The reference standard will be histology or clinical follow-up. A questionnaire regarding patients’ experience with both modalities will also be completed at the end of the follow-up year.

**Discussion:**

Improved treatment options for local site recurrences following CRLM ablation mean that accurate post-ablation staging is becoming increasingly important. The combination of the sensitivity of MRI as a detection method for small intrahepatic lesions with the ability of FDG PET to visualize enhanced metabolism at the ablation site suggests that FDG PET-MRI could potentially improve the accuracy of (early) detection of progressive disease, and thus allow swifter and more effective decision-making regarding appropriate treatment.

**Trial registration:**

Trial registration number:
NCT01895673

## Background

Thermal ablation techniques, including radiofrequency ablation (RFA) and microwave ablation (MWA), are now well-established therapeutic options for the localized treatment of unresectable colorectal liver metastases (CRLM)
[1]. Although potentially curative in selected cases, these techniques carry a risk of incomplete ablation and can show local tumor progression (LTP) rates of up to 30%, of which >95% are diagnosed within one year of ablation
[2-4]. Complete tumour clearance, and therefore potential cure, can still be achieved in patients without extensive intra or extrahepatic metastases through re-treatment of a LTP
[1,5].

Imaging plays a key role in diagnosing progressive disease following hepatic RFA and MWA, with post-ablative lesions generally monitored using contrast-enhanced computed tomography (ceCT) and magnetic resonance imaging (MRI). Without proof of lesion growth from consecutive scans, an important weakness of these modalities is the inability to distinguish between reactive tissue surrounding the ablated lesion (post-ablation effects) and viable tumour
[6]. Diffusion-weighed (DW) MRI outperforms ceCT in the initial detection of small hepatic metastases (<1 cm) and is also superior to ceCT in the detection of CRLM after treatment with systemic chemotherapy without radiation load
[7,8].

Due to the visualization of increased glucose metabolism in tumour cells, fluorine-18 deoxyglucose positron emission tomography (FDG-PET) is a useful tool in the assessment of treatment response following RFA
[6,9]. Ablated lesions that show focal FDG uptake in or within 1 cm of the ablated area are considered clinically suspect for LTP
[6,10]. However, as FDG-PET lacks an anatomical reference it is less accurate in determining the exact location of viable tumour tissue. A solution to this problem was found by combining FDG-PET and CT images to provide fused functional and morphological data
[11], and PET-CT has since been shown to be superior to ceCT in the identification of LTP
[6,9]. Integrated PET-MRI is a new imaging modality, combining the advantages of FDG-PET with the ability of MRI to detect small liver tumours without CT radiation exposure. Recent results show that detection sensitivity for hepatic metastases, through post hoc fusion of FDG-PET images and 1.5 Tesla contrast-enhanced (Gadolinium) MRI obtained from two different scanners, is significantly higher than for PET-CT (93% and 76% respectively, p = 0.02)
[12]. PET-MRI appears to offer higher lesion conspicuity and diagnostic confidence compared to PET-CT
[13], and this additional information can influence clinical management of cancer patients The combined advantages of detection of smaller hepatic tumours with a higher sensitivity and detection of focal FDG uptake suggestive for LTP indicates that PET-MRI could provide complementary information and facilitate improved clinical decision making
[14].

To the best of our knowledge, the effectiveness of integrated PET-MRI in RFA or MWA follow-up has not been investigated. The primary aim of this study is therefore to determine the accuracy of 18 F-FDG PET-MRI in LTP detection. Secondary aims will be to investigate whether PET-MRI is more accurate than PET-CT and ceCT in the detection of new intra-hepatic lesions, and to evaluate inter-observer variability, the impact of PET-MRI on future treatment and patients’ views on both modalities. We hypothesize that PET-MRI will be at least equivalent to PET-CT in the diagnosis of LTP, but superior to PET-CT in the early detection of new intrahepatic lesions and therefore able to positively influence decision making in patients with RFA/MWA-treated CRLM.

## Methods/Design

### Design

This prospective study has been approved by the Medical Ethical Review Board of the VU University Medical Center. The study is investigator-sponsored, independent of industry and is registered at clinicaltrials.gov under number NCT01895673.

### Primary and secondary objectives

We will assess the effectiveness of FDG PET-MRI in the follow-up of thermal ablation (RFA/MWA) of CRLM. Our primary aim will be to assess the accuracy of FDG PET-MRI in the diagnosis of local progression in the first year after RFA/MWA of CRLM. Therefore, all FDG PET-MRI images will be compared to FDG PET-CT and 4-phase liver CT images, which are the current standard of care. Results of different imaging sets will be compared on a per-patient and a per-lesion base. These results will then be compared to a reference standard: either histological outcome (if available) or clinical follow-up.

Secondary outcomes will include the accuracy of diagnosis of new intrahepatic disease after RFA/MWA. Since only a single 18 F-FDG per combined PET-MRI and PET-CT visit will be applied, we will have the opportunity to investigate whether dual-time point PET can increase the specificity of the 18 F-FDG signal and increase diagnostic accuracy
[15]. The reproducibly and robustness of inter-observer variation will also be determined. Clinical relevance will be studied by recruiting a panel consisting of a radiologist, interventional radiologist, nuclear medicine physician, oncologist, oncological surgeon and a radiation oncologist to retrospectively review PET-MRI images and agree on the preferred treatment. Choice of treatment based on PET-MRI will then be compared to the treatment that was actually received based on PET-CT and 4-phase liver CT. Finally, patients’ preferences will be assessed at one year follow-up using a specifically designed questionnaire that compares both modalities (Table 
1).

**Table 1 T1:** Questionnaire comparing PET-CT and PET-MRI (completed following fourth PET-MRI)

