### Study procedure

The standard follow-up protocol during the first year after RFA/MWA of CRLM in the VU University Medical Center consists of three-monthly whole-body FDG PET-CT and 4-phase liver CT, in combination with measurement of serum carcinoembryonic antigen (only when elevated pre-operatively). For the purposes of this study, liver FDG PET-MRI will be added to the routine procedure, using a 3.0 Tesla Ingenuity TF Philips scanner (Philips Medical Systems, Cleveland, OH). This hybrid PET-MRI system is characterized by a sequential acquisition mode and has separate scanners with a turntable patient handling system facilitating patient motion between the MRI and the PET gantries that are located at a 3 meter distance from each other.At the end of one year follow-up, patients will be asked to complete a questionnaire evaluating their experience with the PET-MRI compared to the PET-CT. The study procedure is illustrated in Figure 
1.

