### Image analysis

Only PET-CT and 4-phase liver CT images will be analysed and used in the context of routine patient care during clinical follow-up. The PET-MRI images will not be part of the diagnostic and follow-up process.

For imaging analysis, blinded data sets of all scans will be viewed both separately and independently by two designated, experienced radiologists and two nuclear medicine physicians. The reviewers will be blinded to the results of the other imaging modalities and to final patient outcome. A time-interval of at least four weeks will be introduced between the first and second review. Progressive disease will be scored on a per-patient and per-lesion basis, and results of all imaging modalities will be compared. The criteria for progression on different modalities are defined in Table 
3. Each lesion on each modality will be scored on a separate form and results will be scored from 1–5 (Table 
4) and size and location of the lesions will be reported. A LTP is defined as a lesion located in or within 1 cm of the ablation zone; a new intrahepatic lesion is defined as a lesion located more than 1 cm distant from the ablation zone
[6]. On MRI, a suspicious lesions has to meet the definition of LTP in at least two different sequences before it is considered positive for progression.

**Table 3 T3:** Test positivity criteria for progressive disease on different imaging modalities; ≤1 cm of the ablation zone (LTP) / >1 cm of the ablation zone (new intrahepatic recurrence)

ceCT		Newly detectable hypodense lesion
MRI	T1	New focal hypo-intense lesion
	T2	New focal hyper-intense lesion
	Contrast enhanced	Irregular peripheral enhancement pattern of a circumscribed lesion
	Diffusion weighed	Lesion with high signal intensity on b800
FDG PET		Lesion with clearly increased focal uptake as compared to liver background

**Table 4 T4:** Study form for reviewers’ results (per lesion base)

**Study number:**		**Reviewer number:**
**Score**	**Definition**	**Explanation**
1	Normal	Confident that no tumor recurrence is present in the ablation zone/confident that no new intrahepatic lesions are present
2	Probably benign	The appearance of the ablated lesion is compatible with post-ablational inflammation or rim-like characteristics/the new lesions diagnosed do not appear malignant

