### Recurrent disease and repeated treatment

If recurrent disease is suspected on either 4-phase CT of the liver or on PET-CT, the patient will be evaluated for re-treatment by our multidisciplinary liver board. If either resection of a LTP or chemotherapy is indicated, the patient will be excluded from further participation in the study. If patients are eligible for repeated RFA/MWA treatment of the LTP, study participation will be continued. Patients with new intrahepatic lesions that are eligible for local treatment (surgery or ablation) will remain in the study, as long as the initially ablated area remains unaffected (Figure 
1). Prior to re-treatment with RFA/MWA, several biopsies will be taken from the suspected area for pathological confirmation. To minimize the chance of ‘track seeding’, tract ablation will be performed after the procedure. Extra-hepatic disease will be treated as deemed suitable. If there is any doubt as to whether an imaging feature indicates recurrent disease, the scan will be repeated after 3 months as a confirmation.

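### Management impact is measured as a panel's retrospective choice on PET-MRI against treatment actually received, so a difference cannot be put down to the imaging

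*Protocol article*

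**What the plan says.** The Background section lists among the secondary aims "the impact of PET-MRI on future treatment and patients’ views on both modalities", and the Abstract names the effect on clinical management as a secondary outcome.

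Primary and secondary objectives fixes how this is measured. A panel of six specialties is recruited "to retrospectively review PET-MRI images and agree on the preferred treatment". The comparator is then named: "Choice of treatment based on PET-MRI will then be compared to the treatment that was actually received based on PET-CT and 4-phase liver CT".

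The comparator arises in routine care. Under Recurrent disease and repeated treatment, when 4-phase CT or PET-CT raises suspicion of recurrence, "the patient will be evaluated for re-treatment by our multidisciplinary liver board". In case of doubt, "the scan will be repeated after 3 months as a confirmation". Image analysis keeps the new modality out of care: "The PET-MRI images will not be part of the diagnostic and follow-up process".

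Nothing in the article has the panel also choose a treatment from PET-CT and 4-phase CT.

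**The concern.** A comparison meant to show what an imaging modality does to management should hold everything else constant. Here one side is a stated preference, reached by agreement and after the fact. The other is treatment that was delivered, following a board's evaluation in real time. A discordant case may arise because PET-MRI showed something different. It may also arise because a different group decided, because a preference is not the same as a delivered treatment, or because the treatment rested on a later confirmatory scan than the one the panel reads.

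At stake is the interpretation of one stated secondary aim and of the Background hypothesis that PET-MRI can influence decisions favourably. The missing element is a decision that is never collected, so no later analysis can supply it. Background disagreement could produce apparent changes where the modality has no effect, and it could also hide a real effect.

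**Working it through.** **1. The two sides compared**

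| Feature | PET-MRI side | Comparator side |
|---|---|---|
| Imaging | PET-MRI | PET-CT and 4-phase liver CT |
| Timing | Retrospective | Real time, with a possible repeat scan at 3 months |
| What is recorded | Preferred treatment | Treatment received |
| Who decides | Recruited six-specialty panel | Multidisciplinary liver board; overlap with the panel not stated |

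Only the first row is the effect of interest. The second and third rows differ by construction. The fourth differs unless membership coincides fully. With one observation per side and no panel decision on PET-CT plus CT, the contributions cannot be separated.

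**2. Illustration of size**

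The plan gives no figure for this outcome and no rate of disagreement between decision bodies. The inputs are:

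- n = 20 and p = 0.35, from Sample size calculation. With these, the plan's own chance of at least 5 events reproduces: P(X ≥ 5) = 0.8818, stated as 88%. That figure concerns the number of events, not this outcome.
- Disagreement rate d between two decision bodies when the modality has no effect: assumed, 10% to 20%.
- One decision per patient: assumed.

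Expected spurious changes = (patients facing a decision) × d.

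*Patients facing a decision.* The board evaluates re-treatment only when recurrence is suspected. Using the planning rate as a stand-in for suspicion:

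- Local progression only: 20 × 0.35 = 7.
- Local progression or new intrahepatic lesions, assuming independence: 20 × (1 − 0.65²) = 20 × 0.5775 = 11.6, about 12.
- All patients judged: 20.

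| Patients judged | d = 10% | d = 20% |
|---|---|---|
| 7 | 0.7 | 1.4 |
| 12 | 1.2 | 2.4 |
| 20 | 2.0 | 4.0 |

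The chance of at least one spurious change is 1 − (1 − d)^m for m patients judged:

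- m = 7, d = 10%: 1 − 0.9⁷ = 52%.
- m = 12, d = 20%: 1 − 0.8¹² = 93%.
- m = 20: 1 − 0.9²⁰ = 88% at d = 10%, and 1 − 0.8²⁰ = 99% at d = 20%.

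False suspicion would raise the 7-12, and missed recurrence would lower it. The table shows the order of size under assumed rates and is not an estimate for this trial.

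**The case against.** The strongest reply is that this is one secondary, apparently descriptive outcome in a 20-patient observational study. The text says only that the choices will be compared, and attaches no test, success threshold or attribution rule. The readers' per-lesion forms would also allow each discordant case to be checked against whether the image sets really differed. Retrospective review is unavoidable because PET-MRI is kept out of care, and the proposed repair is retrospective too. These points stand, and they limit the weight of the finding. They do not supply the missing decision on PET-CT plus CT, and checking the readings case by case would not show what the same panel would have chosen on the other images.

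A reader might also infer more than the article supports:

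- *The panel is a wholly different board.* The recruitment wording suggests this, but membership of the liver board is not given. Overlap would remove some or all of the decision-maker difference and leave the others.
- *The panel is unmasked or sees different clinical data.* The masking statement, "The reviewers will be blinded to the results of the other imaging modalities and to final patient outcome", belongs to the four image readers. Silence about the panel in a condensed article is not a defect, because the full protocol may cover it.
- *Treatment received was shaped by patient wishes or fitness.* This is plausible, but the article does not say so for follow-up decisions.
- *Every difference will be credited to PET-MRI.* The article does not say this.

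**Conclusion.** The point holds for the comparison as fixed in the text. Discordance between the panel's choice on PET-MRI and treatment received cannot be attributed to PET-MRI, because timing, preferred versus received treatment and possibly the decision-maker change along with the imaging. The aim of showing how far PET-MRI alters management is therefore not answered cleanly.

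The size is unknown. At an assumed 10-20% disagreement, about 0.7-2.4 spurious changes would be expected among roughly 7-12 patients with recurrence. The figure of 2-4 applies only if all 20 patients are judged, and should not be read as the expected number when only suspected recurrences reach the board. Both ranges rest on a disagreement rate that the documents do not give, and the 7-12 also rests on the planning rate and on independence.

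It would go too far to say that the comparison is uninformative, or that the trial's main conclusion is at risk. The primary accuracy aim is unaffected. This is an inexpensive improvement to a secondary outcome.

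**What to change.** Have the same panel record a decision twice for each case: once on PET-MRI, and once on PET-CT plus 4-phase CT. Provide the same clinical information both times. Mask the panel to treatment received and to outcome as far as practicable; this may be imperfect if members work at the treating centre. Randomise the order of the two image sets and leave at least the four weeks already set between the readers' reviews.

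Report the within-panel proportion of changed decisions with a 95% confidence interval. State whether the unit is the patient or the visit; if it is the visit, the interval must allow for several decisions from one patient. Keep treatment received as a descriptive comparator. Its disagreement with the panel's own PET-CT plus CT choice then shows the background level. Some changes will still reflect the panel's own inconsistency between sessions, and the report should say so.

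The cost is panel time. The images are already acquired, and no new staff or patient procedure is needed. The extra load is 20 case reviews by six specialists, or up to 20 × 4 = 80 if every three-monthly visit is judged. Patient care does not change.

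### The management-impact comparison shows whether the PET-MRI choice differs from the treatment given, not whether the difference is right, so by itself it cannot support a positive influence on decisions

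*Protocol article*

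**What the plan says.** Under Primary and secondary objectives, a multidisciplinary panel is to "retrospectively review PET-MRI images and agree on the preferred treatment". The next step is: "Choice of treatment based on PET-MRI will then be compared to the treatment that was actually received based on PET-CT and 4-phase liver CT". The abstract describes this outcome as "the extent to which FDG PET-MRI alters clinical management", and the Background lists among the secondary aims "the impact of PET-MRI on future treatment and patients’ views on both modalities". Neither description has a direction.

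The hypothesis at the end of the Background does. It expects PET-MRI to be at least equivalent to PET-CT for local tumor progression, superior for early detection of new intrahepatic lesions, and "therefore able to positively influence decision making in patients with RFA/MWA-treated CRLM".

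Histology or clinical follow-up is the reference standard. Primary and secondary objectives and the Discussion attach it to the imaging results; neither attaches it to the treatment choices. Statistical analysis names no method for the panel outcome.

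Two further statements matter here. Image analysis says of the study scan: "The PET-MRI images will not be part of the diagnostic and follow-up process". Recurrent disease and repeated treatment says that when CT or PET-CT raises suspicion, "the patient will be evaluated for re-treatment by our multidisciplinary liver board".

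**The concern.** Disagreement between two treatment choices has no sign. If PET-MRI shows disease that is not there, or misses disease that is, the panel's choice departs from the treatment received just as it does when PET-MRI is right and PET-CT is wrong.

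Wrong-direction changes are plausible in this setting. The Background says that CT and MRI, without proof of growth, cannot separate reactive tissue around the ablated lesion from viable tumour. Because PET-MRI does not enter care, the panel's choices are not acted on, so the later course of treatment does not show whether they were right. Only the reference standard can supply the direction, and the stated comparison does not use it.

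At stake is the reading of the result. A large share of altered decisions, reported as clinical relevance, could be taken as benefit when the net movement toward confirmed disease status is nil or negative.

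**Working it through.** The plan gives no figure for this outcome. Its only calculation is the 88% chance of finding 5 events with n = 20 and p = 0.35. That reproduces as P(X ≥ 5) = 0.8818, but this point does not depend on it.

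**Inputs.** Sensitivities of 93% (fused PET and MRI) and 76% (PET-CT) come from the earlier study of hepatic metastases cited in the Background. Assumption for illustration: a decision is correct when the lesion is detected. Let a be the probability of a correct decision with PET-MRI and b the same with PET-CT.

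**Independent errors.** Changes toward the truth = a(1 − b). Changes away from it = b(1 − a). Discordance is their sum.
- PET-MRI better (a = 0.93, b = 0.76): toward 0.93 × 0.24 = 22.3%; away 0.76 × 0.07 = 5.3%; discordance 27.6%; net +17.0 points.
- PET-MRI worse (a = 0.76, b = 0.93): toward 0.76 × 0.07 = 5.3%; away 0.93 × 0.24 = 22.3%; discordance 27.6%; net −17.0 points.

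**Nested detection** (the better test finds everything the other finds). Discordance = |a − b| = |0.93 − 0.76| = 17.0% in both cases: all toward the truth in the first, all away from it in the second.

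Under either assumption, swapping the better and the worse test leaves discordance unchanged and reverses the net effect.

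**In patients.** Suppose, purely as an assumption, that 6 of 20 choices differ, with one decision per patient. The crude result is 6/20 = 30%. Splits of 6 toward and 0 away, 3 and 3, and 0 and 6 give net figures of +30%, 0% and −30%, all behind the same 30%.

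**Does a less accurate PET-MRI always produce more changes?** Hold b at 0.76.
- Independent errors: discordance is 27.6% at a = 0.93; 2 × 0.76 × 0.24 = 36.5% at a = 0.76; 0.60 × 0.24 + 0.76 × 0.40 = 44.8% at a = 0.60. It rises as accuracy falls.
- Nested detection: 17% at a = 0.93; 0% at a = 0.76; 16% at a = 0.60. It does not.

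**Precision of a directional result.** If all D discordant choices go one way, the exact two-sided p-value is 2 × 0.5^D: 0.0625 for D = 5 and 0.031 for D = 6. The exact 95% lower limit for the proportion going that way is 0.025^(1/D): 47.8% for D = 5 and 54.1% for D = 6. At least six assessable discordant patients, all in one direction, are needed before chance is excluded at the 0.05 level.

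**The case against.** The strongest reply is that the article says only that the choices will be compared. It does not say that the result will be a bare count, and a comparison does not rule out describing the type of each change; such detail may sit in a fuller document. This stands in part. The crude proportion is an inference, although the abstract's wording points to it. What does not depend on that inference is the comparator: it is the treatment received, and the article does not tie this comparison to the reference standard.

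The second reply is that the stated aims are neutral and the outcome matches them, while the hypothesis reaches its positive influence through better detection, which is tested against histology or follow-up. This is correct. A reader might infer that the hypothesis goes untested, or that outcome and aim contradict each other; the document supports neither. But better detection need not change treatment, and the one outcome that looks at that step cannot show which way the change goes.

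A reader might also infer that a worse PET-MRI must yield a larger impact. That holds with independent errors but fails under nested detection.

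Finally, the reference standard gives disease status, not the correctness of a treatment. Two different treatments chosen for the same confirmed disease cannot be scored against it. That stands and limits what the repair can deliver.

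**Conclusion.** The point holds in a limited form. The comparison of the panel's choice with the treatment received carries no information on direction, so by itself it cannot support the claim of a positive influence on decision making. Indirect support through the accuracy results remains.

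The size (27.6% discordance either way with independent errors, 17.0% either way when nested, against a net effect of +17 or −17 points) is illustrative. It rests on equating detection with a correct decision and on sensitivities from post hoc fusion of images from two scanners, not from an integrated system. The 6-of-20 figure is an assumption with no source in the article. The absence of direction itself does not depend on any of these numbers.

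The PET-MRI choice comes from a retrospective panel and the actual treatment decision from the liver board, so some disagreement may not come from the modality at all. This is a secondary outcome in a 20-patient observational study, and the primary accuracy aim is unaffected. It is worth correcting because the correction is small and the misreading is an easy one.

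**What to change.** Add to Primary and secondary objectives, after the sentence on the comparison, wording such as:

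*Each discordant choice attributable to a difference in detected disease will be classified against the reference standard (histology or clinical follow-up) as toward the confirmed disease status, away from it, or not assessable. Different treatments chosen for the same confirmed disease count as not assessable. The number in each class will be reported descriptively with exact confidence intervals, alongside the crude proportion changed. The crude proportion will not be presented as evidence of a positive influence.*

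A formal pass mark on the net proportion is not advised: with 20 patients, six or more one-way changes would be needed to exclude chance.

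The cost is a few lines of text, a short rule for deciding which discordances stem from detected disease, and a tabulation against reference data already collected. The downsides are real. Some changes will be not assessable. Many changes prompted by PET-MRI alone will rest on follow-up rather than histology, because care is guided by CT and PET-CT. The directional result will be imprecise.
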